# Short, Animated Storytelling Video to Reduce Addiction Stigma in 13,500 Participants Across Multiple Countries Through an Online Approach: Protocol for a Randomized Controlled Trial

**DOI:** 10.2196/73382

**Published:** 2025-05-05

**Keywords:** stigma reduction, addiction, health communication, social media, animation, video, storytelling.

## Abstract

**Background:**

Stigma toward people with addiction is a well-documented phenomenon that dramatically impacts help-seeking, treatment, and recovery. Interventions aimed at reducing stigma toward those with addiction must overcome the frequent mischaracterization of addiction as a failure of judgment rather than a chronic, treatable illness. Previous research has demonstrated that social contact with people recovering from addiction can promote empathy and reduce stigma, but social contact is difficult to scale. Short, animated storytelling (SAS) is a novel health communication approach that scales easily because it can leapfrog barriers associated with language, culture, literacy, and education levels.

**Objective:**

This study will investigate the effect of a cross-culturally accessible SAS video intervention aimed at reducing stigma and increasing empathy toward people with addiction. We also seek to gain insight into the mechanisms of action of this SAS intervention by measuring the contribution of sound design to their effect.

**Methods:**

We will conduct a randomized controlled trial with 13,500 adult participants from the United States, the United Kingdom, and South Africa, recruited online via Prolific Academic and randomized into 3 arms, per country. The 2 intervention arms will receive a wordless, social contact–based SAS video, one arm with a soundtrack and one without. The third arm will receive an educational video about addiction. Validated questionnaires will be used to assess our primary outcome, addiction stigma, and secondary outcomes, optimism, warmth toward the subject, and hopefulness, at baseline, immediately post exposure, and 2 weeks later. Ethics clearance was obtained on August 15, 2024, from the Stanford University institutional review board (protocol 76457).

**Results:**

This trial was funded in January 2025 by the Heidelberg Institute of Global Health, the Faculty of Medicine at Heidelberg University, in Germany. As of March 2025, no data have been collected. The estimated start date for this trial is May 15, 2025. We expect to complete data collection by July 1, 2025, and expect results to be published in the spring of 2026.

**Conclusions:**

Here, we present the protocol for an online, multicountry, randomized controlled trial. This trial is designed to measure the effect of an innovative approach to global health communication (wordless, short, and animated storytelling) on addiction stigma in 3 global regions. These findings will inform the design of future scalable, digital health storytelling interventions for global audiences while exploring the capacity of SAS to shift public health attitudes and perceptions. Furthermore, if effective, the intervention described here could be disseminated broadly via social media and other online platforms.

**Trial Registration:**

ClinicalTrials.gov NCT06705205; https://clinicaltrials.gov/study/NCT06705205

**International Registered Report Identifier (IRRID):**

PRR1-10.2196/73382

## Introduction

Stigma toward people with addiction is a well-documented phenomenon that dramatically impacts recovery by discouraging help-seeking behavior, isolating those affected, and increasing the likelihood of shame-related comorbidities such as anxiety and depression [1]. Similar to stigma in other domains, stigma toward people with addiction involves prejudice and discrimination, leading to compounding sequelae such as avoidance, self-stigmatization, and failure to seek treatment [2]. These effects have been documented cross-culturally and globally, worsening an already challenging public health issue [1,2]. The World Health Organization estimates that approximately 400 million people aged 15 years and older live with alcohol use disorders globally [3]. In addition, an estimated 39.5 million people aged 15-64 years are affected by drug use disorders [4]. Recent research suggests that the COVID-19 pandemic dramatically exacerbated these problems, particularly in low- and middle-income countries [5]. In addition, the pandemic aggravated social isolation and loneliness, exacerbating self-stigmatization, especially for underresourced populations that are at a greater risk of addiction [6-8]. Stigma can thus significantly widen health disparities, underscoring the need for effective interventions to ameliorate it.

Reducing addiction stigma is challenging because addiction is often viewed as a failure of judgment and lack of morality rather than a chronic illness, with complex causes (genetic and environmental) that require both medical and psychological intervention. Interventions aimed at reducing public stigma toward those with addiction must address this frequent mischaracterization of addiction [9]. Evidence of stigma has even been documented among health care professionals with observed negative impacts on quality of care [10]. Previous research has demonstrated that social contact with people recovering from substance use disorders can promote empathy and reduce stigma, but these interventions often require extended face-to-face interaction and are difficult to scale [11]. Intergroup social contact interventions, despite their promise for reducing stigma, can also be limited by individual selection bias, due to the very prejudice the intervention aims to reduce [12]. A further challenge lies in the fact that public health communication interventions often result in the systematic exclusion of non–English speakers and non-Western cultural groups [13]. Even scalable virtual interventions for stigma reduction and empathy building have produced mixed findings beyond high-income and homogeneous populations [14]. As a result, there is an urgent need for novel approaches that focus on broadly disseminating accessible, positive stories related to addiction to promote empathy and understanding. The major challenge lies in making them accessible across languages, cultures, education, and literacy levels.

Short, animated storytelling (SAS) is a novel health communication approach developed in response to the need for rapid, global dissemination of public health messaging across various languages, cultures, literacy, and education levels during the COVID-19 pandemic [15,16]. SAS interventions boost cross-cultural relevance through accessible character designs [17], and they support the engagement of diverse audiences through the use of wordless visual storytelling and compelling soundtracks [18,19]. These interventions are specifically designed for online environments, namely social media platforms, where people readily consume short video content and increasingly seek health information [20]. Social media has become a critical tool for public health communication, with a growing body of research evaluating these interventions [21]. The global reach of many social media platforms enhances their potential utility for scaling health communication interventions, including those aimed at reducing addiction stigma. However, such interventions must be rigorously tested in different global regions and their mechanisms of action must be better understood in order to inform the ongoing development of effective, scalable, and cross-culturally accessible interventions.

This study will investigate the effect of a globally accessible SAS video intervention aimed at reducing stigma and increasing empathy toward people with addiction. In addition, we will attempt to isolate and quantify the contribution of sound design to the effect of the intervention. This wordless, animated SAS intervention was co-created with a multidisciplinary team of experts who are trained in health communication, addiction medicine, animation, sound design, screenwriting, and digital storytelling. The video was designed to resonate globally, across cultures, and traverse linguistic, literacy, and educational barriers. We hypothesize that a single exposure to the 2.5-minute intervention video will measurably reduce addiction stigma and boost hope, optimism, and empathy toward people with addiction in three culturally distinct global settings: the United States, the United Kingdom, and South Africa. We also hypothesize that this effect will persist at a 2-week follow-up and that sound design will enhance the magnitude and durability of the observed effect.

## Methods

### Study Setting, Participants, and Recruitment Procedure

This study will be conducted online. Adult participants from the United States, the United Kingdom, and South Africa will be recruited and randomized through the platform Prolific Academic (ProA). These 3 countries were chosen because Prolific has a large enough number of participants in each of these countries to make it feasible to reach our desired sample size. The video intervention and questionnaires will be delivered to participants through the secure, online survey platform, Qualtrics, an experiment builder that provides users with the tools for undertaking online behavioral research.

We will enroll 4500 participants in the United States, 4500 participants in the United Kingdom and 4500 participants in South Africa using ProA, a crowdsourcing platform frequently used to conduct rigorous academic research [22]. Participants in this study will be adults aged 18-49 years. This age group is selected because they reflect our target audience: adults who are likely to seek information and regularly engage on social media [23]. Broad eligibility criteria reflect our interest in evaluating the intervention as it would be delivered outside of experimental conditions: online, widely available via social media or the Internet, and not targeted toward any specific audience. Before enrolling in the study, all participants will read an information sheet on ProA that has been approved by the Stanford Ethics Committee. Those who agree to participate will be directed by Prolific to complete the study activities on Qualtrics.com, a secure online data-collection platform.

### Randomization, Consent, and Study Design

After reviewing the Institutional Review Board-approved information sheet, delivered to prospective participants online via ProA, those who indicate their consent to take part in the study will then be randomly assigned to one of three groups:

Intervention A: receiving the SAS video full intervention group.Intervention B: receiving the SAS video partial intervention (without sound) group.Control Group: receiving written information about addiction prevalence.

A baseline survey will be used to collect demographic information as well as baseline data on our primary and secondary outcomes. Thereafter, the Intervention A group will watch the 2.5-minute video, the Intervention B group will watch the 2.5-minute video without sound, and the control group will read a fact sheet about the global burden of addiction. Following this, all groups will complete a series of validated questionnaires to assess our primary outcome: addiction stigma, and secondary outcomes: optimism, warmth toward the subject, and hopefulness.

We will conduct the first round of surveys immediately post exposure of the intervention groups to the SAS video interventions and the control group to their written fact sheet. Follow-up assessments, using the same surveys, will be conducted 2 weeks later. To ensure the accuracy and validity of the results, we will include attention checks and exclude participants who fail these checks. Each participant will spend approximately 8 minutes watching the intervention and completing the surveys and will receive US $4.80 for completing the study. Figure 1 represents the trial design and flow.

**Figure 1 figure1:**
[figure not shown]
Trial design and flow.

### Intervention

This short, animated story video was co-created by a global health communication specialist with formal training in screenwriting and story development, an addiction medicine specialist, a professional animator living in South Africa, an adolescent composer and sound designer, and a group of high school student advisors at Avenues the World School in New York City. The intervention follows a classical 3-act story structure, with an inciting event, rising action, a midpoint, climax, and resolution. Figure 2 displays selected scenes from the SAS intervention video, with corresponding timestamps and descriptions of the story “beats” that propel the narrative forward. The main character is a fish who discovers and tries a foreign substance, ignoring the warnings of a more senior fish character. The young fish soon becomes addicted to the substance, and we see the negative impact on his underwater life. He injures others around him while under the influence and, finally, injures himself in his desperate pursuit of the next high. In this way, the video visually conveys the concept of drug tolerance. In the second half of Act 2, the main character, in desperation, gulps down the remaining dose of the addictive substance before realizing that he is (literally) hooked. A fishing line drags him off-screen and it seems that all is lost until the senior fish reappears and helps him break free of the hook. This leaves a deep gash in the young fish’s mouth. In the young fish’s moment of deepest pain and shame, the senior fish reveals his identical gash (the unexpected story twist). The 2 fish share a moment of painful empathy, then swim off-screen together. The only words in this video appear as text on the final, “call-to-action” screen: “Hooked on something that’s hurting you? Speak up. There’s help.” The video can be viewed on YouTube [24].

**Figure 2 figure2:**
[figure not shown]
Selected scenes from short, animated storytelling intervention with timestamps.

### Primary Outcome

The primary outcome is stigma toward people with addiction, which we will measure using an abbreviated, 18-item version of the Attribution Questionnaire (AQ-18) [25,26]. This version (AQ-18) includes the blame, pity, help, dangerousness, fear, and avoidance subscales of the original questionnaire, as these subscales are most appropriate, in scope and topic area, to detect a potential effect of our short video “micro-intervention.” The AQ-18 will be scored along a 9-point Likert scale indicating the extent to which participants agree with the item ranging from “not at all” (1) to “very much” to (9) with a maximum score of 27 for each 3-item construct. Higher scores indicate greater stigma. The AQ-18 is highly reliable and subscales have Cronbach *α* ranging from fair (0.6, responsibility) to good (0.93, fear/dangerousness) [25,26]. Participants responding to the AQ-18 may score between 12 and 108. Like the longer version, the AQ-18 offers a brief vignette, which we modified to be (1) gender-neutral and (2) about addiction rather than general mental illness. All participants will read the following vignette before completing the questionnaire. A gender-neutral name (Alex) was chosen to eliminate potential gender bias:

Alex is a 30-year-old with a history of addiction. Alex’s substance use problem has harmed Alex’s health and hurt others. Alex has been hospitalized several times for addiction-related health problems.

### Secondary Outcomes

#### Optimism

We will measure optimism using the Brief García’s Interactive Optimism Scale (BIOS-G) [27]. The BIOS-G is an instrument designed to assess an individual’s level of general optimism toward their life and other people. The scale includes 4 statements for which respondents indicate their level of agreement from 1 (“Of course not”) to 4 (“Yes, of course”). Higher scores indicate a greater level of optimism. Participants may score between 4, (indicating low optimism) and 16, (indicating high optimism). The BIOS-G has demonstrated reliability and validity across diverse populations, with a reported Cronbach *α* of 0.86 [27].

#### Attitude

We will also measure attitudes toward those with addiction using a “stigma thermometer,” a tool we previously developed to assess attitudes regarding sexual orientation and gender diversity [28]. The thermometer provides the following prompt:

Using a scale from zero to 100, please tell us about your personal feelings toward people who are addicted to substances such as drugs or alcohol. As you do this task, think of an imaginary thermometer. The warmer or more favorable you feel toward people who are addicted to substances such as drugs or alcohol, the higher the number you should give it. The colder or less favorable you feel, the lower the number. If you feel neither warm nor cold toward people who are addicted to substances such as drugs or alcohol, rate it 50.

Researchers in the fields of political science and psychology have frequently used feeling thermometers to assess attitudes toward stigmatized groups [29].

Finally, we will measure subjective levels of hope using a visual analog scale (VAS), a longstanding, validated tool for assessing related constructs of stress and subjective well-being [30]. The VAS provides the following prompt:

Using a scale from zero to 100, please tell us about how hopeful you feel after watching the video [control group participant instructions will reference the fact sheet in the AQ-27 instead]. As you do this task, think of an imaginary thermometer. The more hopeful you feel, the higher the number you should give it. The less hopeful you feel, the lower the number. If you feel neither hopeful nor hopeless, rate it 50.

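### The hope item presupposes an exposure that has not happened at baseline, is ambiguous at two weeks, and names different material in the video arms than in control

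*Protocol article*

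**What the plan says.** Hopefulness is one of the named outcomes: "secondary outcomes: optimism, warmth toward the subject, and hopefulness" (Randomization, Consent, and Study Design). The Attitude section prints the item in full. After introducing the 0-100 scale it asks "how hopeful you feel after watching the video [control group participant instructions will reference the fact sheet in the AQ-27 instead", the bracketed part being the note on the control version. The rest of the prompt, including the neutral anchor at 50, is printed once for everyone.

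On timing, the Abstract lists the outcomes "at baseline, immediately post exposure, and 2 weeks later". The study design section agrees: "A baseline survey will be used to collect demographic information as well as baseline data on our primary and secondary outcomes". Exposure comes next: "Thereafter, the Intervention A group will watch the 2.5-minute video", while controls read their fact sheet. The same section says the two-week follow-up reuses the same surveys. The Analysis section then compares hope between the video arms and control at T1 and again at T2.

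**The concern.** An outcome that is measured repeatedly and compared between arms should ask the same question of everyone on each occasion. This item does not. Its wording depends on having seen something, and on which material was seen. Three things are at stake: whether a baseline hope score can exist at all, whether T1 and T2 scores measure the same thing, and whether a video-versus-control difference reflects the intervention alone or partly the way the question was put. Raising hope is one of the hypotheses in the Introduction, and the trial is sized for a very small standardized difference (d = 0.1), so modest measurement differences could matter.

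**Working it through.** No figure in the plan bears directly on this point. The check is mainly a reading of the sections against each other.

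**Step 1: the item at each time point.**

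| Time | What participants have seen | What the printed item asks | Result |
|---|---|---|---|
| Baseline | Nothing | Hope after the video (control: reference to the fact sheet) | Cannot be answered |
| T1 | Video or fact sheet, just now | The same | Answerable, but the material named differs by arm |
| T2 | Video or fact sheet, two weeks ago | The same | Recalled reaction or present hope; the material named still differs by arm |

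No baseline version of the item is given. It is hard to suppose that one exists elsewhere, because the section on access to the full protocol says that this article is the full protocol, and the prompt is reproduced word for word.

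**Step 2: which contrasts are touched.** There are three pairwise contrasts: A versus control, B versus control, and A versus B. The wording differs in the first two. Arms A and B receive the same prompt, so the estimate of the contribution of sound carries no arm-dependent wording.

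**Step 3: which outcomes are touched.** The AQ-18 vignette is read by all participants and does not mention the exposure. The printed feeling-thermometer prompt does not mention it either, and the optimism scale is described as general optimism. Only hope is affected.

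**Step 4: which analyses need a baseline.** The Analysis section compares arms at T1 and at T2. Under 1:1:1 randomization those comparisons need no baseline. Change from baseline, or adjustment for baseline hope, would need one. The methods listed for secondary outcomes also include matched t tests and repeated-measures ANOVA. Used across time, these assume that the item keeps its meaning.

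**Step 5: could a wording shift matter?** The documents give no size for one, so this is illustration only. Assume no true effect and a shift of b standard deviations in favour of video, caused by wording alone. Take the one-sided 0.01 level from the Sample Size section. The chance of a false rejection for one video arm against control is Φ(b × √(n/2) − 2.326), with n per arm. With 1500 recruited per arm per country and 20% attrition, n = 1500 × 0.8 = 1200 in one country and 3 × 1200 = 3600 pooled. For b = 0.05 and n = 1200: 0.05 × √600 = 1.225, then 1.225 − 2.326 = −1.10, and Φ = 0.135.

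| Assumed shift (SD) | n = 1200 | n = 3600 |
|---|---|---|
| 0.02 | 3% | 7% |
| 0.05 | 14% | 42% |
| 0.10 | 55% | 97% |

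The nominal rate is 1%. A shift in the other direction would instead hide a true benefit. The range runs from minor to dominant, and nothing in the documents says where the truth lies.

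**The case against.** The best defence concerns comparability. A control participant cannot be asked about a video that was never shown, so naming the material each arm received is a parallel adaptation. The phrase can be read as a time marker for present hope rather than a request to rate the material. The contrast between a story and burden statistics is the randomized exposure itself, and the response scale and anchor are common to all arms. This stands in part: an artefact is possible but not demonstrated. It does not remove the problem, because a neutral prompt would have served every arm, as the feeling thermometer shows. It also does not touch the baseline contradiction or the ambiguity at T2.

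Several stronger readings are tempting, and the documents do not support them:

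- *Hope is not comparable between any arms.* The two video arms share their wording.
- *Without a baseline, hope cannot be analysed.* Randomized comparisons at T1 and T2 do not depend on one.
- *The arm-specific item unblinds the analysts.* The bracket describes on-screen instructions. Nothing says that hope would be exported under arm-labelled variables, and a single coded column would reveal nothing.
- *The artefact equals the whole effect the trial is sized for.* One can get there by assuming a 2-point shift and an SD of 20 to 25 (2/25 = 0.08; 2/20 = 0.10). Neither value is in the documents, and a 0.5-point shift would give only 0.02 to 0.025.
- *The AQ-27 reference means the wrong instrument is used.* The Primary Outcome section is clear that the instrument is the AQ-18; the reference is an editorial slip.

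**Conclusion.** The point holds in a limited form. Firmest is the contradiction between a prompt that presupposes exposure and a schedule that collects hope before any exposure; this rests on the text alone. The ambiguity at T2 follows from reusing the same item two weeks later. The arm-dependent wording makes a measurement artefact possible in the video-versus-control comparison of hope, of unknown size and direction. The illustrative rejection rates rest wholly on assumed shifts and should not be quoted as estimates.

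The reach is one single-item measure among three secondary outcomes, and two of its three pairwise contrasts. No primary conclusion depends on it. It should be corrected, because the repair is simple and the flaw cannot be undone once responses are collected.

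**What to change.** Before launch, replace the hope item with one exposure-neutral prompt, identical in all arms at baseline, T1 and T2, for example: *how hopeful do you feel right now*. Keep the 0-100 scale and the anchor at 50. Delete the arm-specific bracket, and the AQ-27 reference goes with it.

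Declaring hope a post-exposure measure with no baseline would also settle the scheduling contradiction. It would leave the arm-dependent wording and the ambiguity at T2 in place, so it is the weaker choice.

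The cost is one reworded survey item, with no change to sample size, schedule or analysis. The article reports that no data had been collected as of March 2025. If the item has since been fielded, the exact wording shown in each arm at each time point should be reported, and the video-versus-control result for hope read with that caveat.
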